# Effect of home-based transcranial direct current stimulation (tDCS) on cognitive function in patients with mild cognitive impairment: a study protocol for a randomized, double-blind, cross-over study

**DOI:** 10.1186/s13063-019-3360-1

**Published:** 2019-05-21

**Keywords:** Transcranial direct current stimulation, Mild cognitive impairment, Home-based, Cross-over study, Brain stimulation

## Abstract

**Background:**

The possible effect of transcranial direct current stimulation (tDCS) in improving cognitive function is clear from studies involving pre-dementia stage mild cognitive impairment (MCI). However, the application of tDCS in actual clinical practice entails repeated hospital visits almost every day for treatment. The objective of this study is to confirm the possibility of self-application of tDCS at home by elderly patients with declined cognitive function and the significant clinical effect of tDCS administered at home.

**Methods/design:**

This study will be conducted in 20 elderly people aged 60 to 80 years with complaints of subjective memory impairment while maintaining general functions with limited activities of daily living. This study involves a cross-over design that will include 2-week active or sham stimulation of both dorsolateral prefrontal cortexes (left, anode; right, cathode) randomly with a 2-week wash-out phase. Changes in cognitive function will be evaluated using visual recognition tasks and neuropsychological tests. In this study, tDCS will be carried out by each patient at his/her home and its safety and suitability will be evaluated.

**Discussion:**

In this study, patients will apply a portable tDCS, developed for home use, for more than 2 weeks. Such studies can contribute to the use of tDCS as a realistic therapy. In addition, the utility of home-based tDCS will be confirmed by application of tDCS at home by the elderly with declined cognitive function. Furthermore, confirmation of tDCS as a significant therapeutic method can facilitate treatment of Alzheimer’s dementia at an early stage, including MCI.

**Trial registration:**

Clinical Research Information Service (CRIS), KCT0002721. Registered on 9 March 2018.

**Electronic supplementary material:**

The online version of this article (10.1186/s13063-019-3360-1) contains supplementary material, which is available to authorized users.

## Background

Mild cognitive impairment (MCI) refers to declined cognitive function below normal range while maintaining successful independent daily living [1]. Declined cognitive function in MCI falls between cognitive deterioration caused by aging and dementia due to Alzheimer’s disease or other [2]. MCI might be a precursor to dementia [3], which is an important topic for clinical trials investigating dementia treatment and prevention. Transcranial direct current stimulation (tDCS) is a therapeutic modality indicated for declined cognitive function, including MCI.

tDCS is used to control neuronal excitability by transmitting a small amount of current via an electrode patch on the scalp. Anodal stimulation increases cortical activity by drawing the resting potential close to the threshold potential while cathodal stimulation inhibits excitability by separating the resting potential from the threshold potential [4]. As control over brain activity affects brain functions such as behavior, emotion, and information processing, clinical application of tDCS for depression, multiple sclerosis, and other central nervous system disorders is under investigation by several clinical groups [5–7].

The effect of tDCS on cognitive function has been established in various clinical trials and experimental studies. In a study conducted in healthy adults, visuospatial working memory performance status improved after anodal tDCS [8]. Another study has shown that tDCS can result in temporary but meaningful improvement in aging-related cognitive decline [9]. In tDCS and repeated transcranial magnetic stimulation (rTMS) studies conducted in individuals with declined cognitive function, improvement of cognitive function has been reported [9–13]. In a study by Meinzer et al. [11] in particular, anodal tDCS increased task performance and reversed pathological brain activity and connectivity patterns. Boggio et al. [13] confirmed that the performance in visual memory recognition task is improved after tDCS treatment of dorsolateral prefrontal cortex in a study of patients with Alzheimer’s dementia. In these studies, tDCS has been applied temporarily or without sufficient repetition. Therefore, it is necessary to evaluate the effect of repeated tDCS sessions on cognitive function in patients with MCI.

tDCS is user-friendly, relatively cheap, and tolerable compared to similar non-invasive brain stimulating devices such as rTMS [14]. In addition, no serious side effects have been reported with tDCS, thus encouraging home use [15]. In fact, home-based clinical application of tDCS has been investigated in a number of studies in depression, chronic pain, multiple sclerosis, tinnitus, and mild vascular dementia [16–20]. However, to the best of the author’s knowledge, home-based clinical application of tDCS has not been investigated in MCI. Furthermore, the same equipment used in hospitals is also used in previous home-based tDCS studies. Therefore, the development of smaller, low-weight, and automated devices and additional studies investigating the suitability and safety of home-based application are needed.

This study will investigate the effect of tDCS on cognitive function and the safety of self-application by instructing patients with MCI to self-administer tDCS repeatedly using the device developed for home-based application. This study is designed to determine whether repeated tDCS stimulation at home can improve cognitive function by visual recognition task and neuropsychological tests in patients with MCI. It will also determine whether patients with MCI can safely administer tDCS by themselves at home.

## Methods/design

This study will involve patients diagnosed with MCI who visited Gangnam Severance Hospital and Severance Hospital, tertiary referral centers and the teaching hospital of Yonsei University. All participants will be informed of experimental goals of this study. Written informed consent will be obtained. This study protocol was approved by the Korean Ministry of Food and Drug Safety and complied with ethical standards based on Declaration of Helsinki.

### Inclusion criteria

Selection criteria are: 1) adults aged between 60 and 80 years; and 2) patients with cognitive decline from previous performance levels but which do not interfere with capacity for independence in everyday activities. Cognitive decline but not dementia will be determined using the Korean version of the Global Deterioration Scale (GDS; 2–3 points) [21] or Clinical Dementia Rating (CDR; if 0.5) and MMSE-DS (Korean version of MMSE for Dementia Screening; higher than the cut-off according to age and academic background) [22]. Independence in activities of daily living will be determined according to Seoul-Instrumental Activities of Daily living score [23] (< 7 points). Complaints of cognitive decline induced by depression will be evaluated using K-GDS (Korean version of Geriatric Depression Scale) (≤ 8 points) [24]. Final clinical diagnosis will be conducted by skilled psychiatrists using DSM-V (Diagnostic Statistical Manual of Mental Disorder, fifth edition) criteria for mild neurocognitive disorder.

### Exclusion criteria

Exclusion criteria are as follows: 1) history of dementia or intellectual disability; 2) use of cognitive enhancers (donepezil, rivastigmine, galantamine, and memantine); 3) reversible medical conditions associated with potential cognitive impairment (e.g., history of vitamin B12 deficiency or hypothyroidism); 4) diagnosis of current alcohol dependence or DSM-V [25] disorders associated with the use of alcohol; 5) epilepsy; 6) clinically severe disorders involving cardiovascular, digestive, respiratory, endocrine, and central nervous systems; 7) history of cerebrovascular surgery; 8) problems associated with direct current stimulating electrode caused by scalp malformation, inflammatory reaction, or other dermatological problem; and 9) other contraindications for tDCS medical device (e.g., metal plate inserted into cephalus, etc.). In addition, patients who participated in other clinical studies within the past 30 days, who expressed difficulty in reading or having a conversation due to vision and hearing issues after wearing assistance, and those who are ineligible for this study based on other medical judgment will be excluded from this study. Use of other psychiatric medication except cognitive enhancers and general medications will be permitted.

### Outcome measures

#### Primary outcomes

This study will determine cognitive improvement by using visual recognition tasks similar to those described previously [12, 13] in which tDCS is administered to patients with Alzheimer’s dementia. In the encoding phase, screens with two, four, six, and eight stimulations are displayed for 10 s, respectively. Participants are required to memorize pictures displayed on each screen. After a 1-s interval, the test phase is started and the specific stimulus is displayed. Participants are required to respond as rapidly as possible whether or not the stimulus involves the picture seen in the encoding phase. Similar to previous studies, our task comprises an encoding phase and a test phase. In contrast to previous studies, black-and-white icon stimuli will be used to provide a more intuitive and simple format. Objects, human body parts, and animals that are generally seen in daily life will be used. The test phase will comprise three, six, eight, and ten test trials of two, four, six, and eight pictures, respectively, in the encoding phase.

#### Secondary outcomes

In addition to visual recognition tasks, standardized neuropsychological tests and questionnaires will be used to determine cognitive improvement and changes in daily life, which will be assessed by 1) letter-number sequencing; 2) spatial span; 3) clinical global impression (CGI) [26]; 4) neuropsychiatric inventory [27]; and 5) Korean version of the Consortium to Establish a Registry for Alzheimer’s Disease Neuropsychological Assessment Battery (CERAD-K) [28].

#### Covariate measures

Additionally, a questionnaire will be used to determine factors that influence the therapeutic utility of tDCS. The questionnaire includes the following: 1) Edinburgh Handedness Inventory [29]; 2) State Anxiety Inventory (STAI-X-1) [30, 31]; 3) Montgomery-Asberg Depression Rating Scale (MADRS) [32, 33]; 4) Korean version of the Hamilton Depression Scale (K-HDRS) [34]; and 5) Hamilton Anxiety Scale (HAM-A) [35].

### Intervention

#### tDCS stimulation protocol

The electrode will be located by placing the anode and cathode on the left dlPFC (F3) and the right dlPFC (F4), respectively, similar to the procedure described by Boggio et al. [13]. To facilitate placement of the electrode at home, a skilled investigator will provide a picture of a desirable location taken with a smart phone. Similar to previous studies [12, 13, 36], active stimulation will increase the current for 30 s. The current is then kept at 2 mA for 29 min. The current is then decreased for 30 s. Sham stimulation will be maintained for 29 min without current flow by increasing current for 30 s followed by a decrease for 30 s. Both conditions will be self-administered by the subject for 30 min each day for 14 consecutive days.

#### Home-based tDCS device

This study will be conducted using a tDCS device (Ybrain, MINDD STIM, http://www.ybrain.com/) designed for application at home. The device consists of 1) a docking station for stimulation setup and information output, 2) a miniaturized module for saving the performance record that is compatible with a smart phone, and 3) a smart phone. The module works with any smart phone, although we will use a research smart phone to control the experimental environment. The module transfers the stimulation performance records to a server linked to the docking station via a compatible smart phone that can be remotely monitored by the investigator. The electrode of the device, which is circular in form and measures 67 mm in diameter (or 22 mm thick) will be used after inserting a disposable sponge into the patch supporter followed by treatment with saline solution. The electrode will be inserted into the pre-selected hole of the cap for fixing on the head and linking to the module (Fig. 1).

**Fig. 1 Fig1:**
[figure not shown]
Image of the device provided to study participants. **a** Module and electrode while wearing cap. **b** tDCS module and electrode. **c** Smart phone with application

#### Safety strategy for home-based tDCS application

Several technologies will be used to safely conduct tDCS independently at home. The stimulation protocol is not modifiable in the module by the subject as it is accessible only with a password via the station. The module contains a skin-contact recognition function. Therefore, the device automatically starts upon recognition of the patch adhering to the skin. The output automatically stops upon recognition of the patch being detached from the skin, even during stimulation. The device stops immediately when the current output exceeds the limit allowed by the module. A smart phone application detects module operation. A self-inspection questionnaire for safety assessment will be administered upon completion of the operation. In addition, 24-h contact information is provided via the smart phone. In case of any suspected side effects, the subject is expected to visit the hospital immediately.

#### Training and support for participants

Even though the device has a safety guarantee, it might be meaningless if the user is not familiar with its usage. Therefore, checklist-based training will be conducted by using the device for practice without stimulation. Subjects who have completed all items of the checklist will be allowed to use the device for the study after three training sessions and the final test. Remote support will be provided via a remote-control program integrated in the smart phone and video calling will be used to facilitate the study.

### Design and procedure

#### Trial design

This study was designed as a 9-week, multicenter, randomized, double-blinded, cross-over clinical study. All subjects will undergo a 2-week treatment phase twice (treatment I and treatment II) with a 2-week washout period. A follow-up assessment will be conducted 2 weeks after completion of the second treatment phase (treatment II; Fig. 2). In treatment I, either active or sham tDCS will be administered. In treatment II, tDCS under different conditions will be administered.

**Fig. 2 Fig2:**
[figure not shown]
Study design and method

**Fig. 3 Fig3:**
[figure not shown]
Schedule of enrolment, interventions, and assessments

#### Randomization and blinding

A random group assignment list was created by statisticians who are not involved in data collection using PASS 12 (NCSS, LLC, Kaysville, Utah, USA, https://www.ncss.com/). Participants are allocated 1:1 to the active first group and sham first group. The device manager will set up the device according to the assignment list in order of participant’s registration number. The same single device can be set to sham or active status using the administration menu. Because only the device manager, who will not contact the participants, knows the assignment list and the password required to access the administration menu, other investigators and participants will remain blind to it. This masks investigators and enables the use of fewer devices.

#### Study schedule

Assessments at each visit are listed in Table 1 & Fig. 3. Details of each phase are as follows:Screening phase: Only participants with written consent will be screened. Subjects who meet the inclusion criteria will be randomized.Treatment phase I (visit 1 to visit 2): During visit 1 (T1), a visual recognition task and a neuropsychological test will be conducted with baseline data for efficacy assessment. After the outcome measures are taken, including covariance measurements, training for tDCS use will be conducted for subjects or their caregivers by using a tDCS device for practice and a check list. The first clinical device application and assessment of side effects will be conducted for subjects who have passed the test for tDCS use. Starting from the day after the first visit, the subject (or his/her caregiver) will use the device once daily for 2 weeks (a total of 14 days). It is recommended to use the device at specific times (e.g., immediately after face washing in the morning). Information about time and period of application by the subject are automatically saved in the device. Researchers will monitor the information remotely at certain times of the day and will call if tDCS is not applied.Wash-out phase (visit 2 to visit 3): The subject will be required to visit the hospital 2 weeks after visit T1 for efficacy assessment. Subsequently, appropriate use of the device by subjects will be assessed by the investigator using a tDCS device for practice. A log of the returned device will be printed by the device manager for records so that blinding is maintained. Later, a 2-week wash-out phase will be conducted.Treatment phase II (visit 3 to visit 4): The subject will be required to visit the hospital at 4 weeks after visit T1. Similar to treatment I, training sessions will be conducted and proficiency with the device will be assessed. Also similar to treatment 1, the device will be used at home after returning from the hospital. After returning home, subjects will apply the device once daily for 2 weeks (14 days).Follow-up phase: Subjects will be asked to visit the study institution at 6 weeks after visit T1. Appropriateness of device application and efficacy assessment will be evaluated by the investigator. Finally, a follow-up assessment will be conducted during a study visit at 2 weeks after the last treatment visit (T4).

**Table 1 Tab1:** List of tests conducted at each visit

Phase	Screening	Treatment I	Washout	Treatment II	Follow-up	
Day	0	1	14	28	42	56
Visit	S1	T1	T2	T3	T4	F1
Visual recognition task		O	O	O	O	O
Neuropsychological test^a^		O	O	O	O	O
Basal symptom and sign	O	O	O	O	O	O
Vital sign^b^	O	O	O	O	O	O
MMSE-DS/GDS/CGI^c^/CGS/S-IADL/K-GDS	O	O	O	O	O	O
Questionnaire^d^		O	O	O	O	O
Concomitant medication check	O	O	O	O	O	O
Adverse event check		O	O	O	O	O

^a^Neuropsychological tests: CERAD, letter number sequencing, spatial span

^b^Sitting systolic/diastolic blood pressure, pulse, and temperature were measured

^c^CGI: not measured at screening

^d^Questionnaires for investigator, subject, and guardian were administered for efficacy assessment

For investigator: MARDRS/HAMD/HAMA

For subject: STAI/PSQI/Hand Function Rating Scale

For guardian: NPI

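### The trial asks whether patients with MCI can apply tDCS themselves at home, yet the schedule lets caregivers apply it and the described session log does not show who did

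*Protocol article*

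**What the plan says.** Four places in the article make the patient the operator. The Abstract's background gives the objective as to "confirm the possibility of self-application of tDCS at home by elderly patients with declined cognitive function". The Abstract's methods add that "tDCS will be carried out by each patient at his/her home and its safety and suitability will be evaluated". The Background section states "It will also determine whether patients with MCI can safely administer tDCS by themselves at home". The tDCS stimulation protocol section states "Both conditions will be self-administered by the subject for 30 min each day for 14 consecutive days".

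The Study schedule says something else. At the first treatment visit, "training for tDCS use will be conducted for subjects or their caregivers". For home use in treatment phase I, "the subject (or his/her caregiver) will use the device once daily for 2 weeks (a total of 14 days". For treatment phase II the text returns to subjects only: "After returning home, subjects will apply the device once daily for 2 weeks (14 days".

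On the record of use, the same section says "Information about time and period of application by the subject are automatically saved in the device". Patients' handling of the device is also checked in clinic. The training section requires a completed checklist, three training sessions and a final test. The Study schedule adds a test before first use and assessments of device use at the later treatment visits.

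**The concern.** Whether cognitively impaired patients can run the treatment themselves is a stated objective, and in the Abstract it comes before the clinical effect. If a caregiver may place and start the device, a full set of logged sessions shows that the household managed the treatment. It does not show that the patient did. The Discussion goes on to argue from use by elderly people with cognitive decline to use by patients without cognitive impairment, and it describes the treatment as self-administered. Sessions run by a caregiver do not support either step.

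The operator wording also differs between the two periods of the cross-over, so a site following the text could handle caregiver help differently in each.

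**Working it through.** **1. The plan's own figure.** The only calculated figure is the sample size, which this point does not depend on. Inputs from the Sample size section: difference 11.61, SD 11.62, α = 0.05 (taken as two-sided), power 90%, dropout 30%. For a two-period cross-over, the noncentrality is 11.61 / (11.62/√N) with N − 2 degrees of freedom. Power is 87.6% at N = 12, 90.6% at N = 13 and 92.9% at N = 14. The smallest even N reaching 90% is 14, and 14 / (1 − 0.30) = 20. Both stated figures reproduce, and neither changes.

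**2. The operator, section by section.**

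| Place | Who operates the device |
|---|---|
| Abstract, background and methods | patient |
| Background | patient, unaided |
| tDCS stimulation protocol | subject, both conditions |
| Study schedule, training at first treatment visit | subject or caregiver |
| Study schedule, phase I home use | subject or caregiver |
| Study schedule, phase II home use | subject (caregiver not mentioned) |

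These are positive statements that conflict. They are not details left to a fuller document. The phase II text also says that the procedure resembles phase I, so whether the caregiver permission carries over is open.

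**3. What the described record can separate.** The log holds time and period. The skin-contact function in the safety section detects a patch on skin, not who placed it. Scheduled home sessions are 20 × 14 = 280 per period and 20 × 2 × 14 = 560 in all (14 × 28 = 392 for 14 completers). The explicit caregiver permission covers the 280 in phase I, and all 560 if it carries over.

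**4. Illustration.** The article gives no caregiver share, so the shares below are assumptions. Suppose that all 20 participants have complete logs and that a share q relied on a caregiver. The number who truly self-applied is k = 20(1 − q). The exact 95% interval runs from the 2.5% quantile of Beta(k, 21 − k) to the 97.5% quantile of Beta(k + 1, 20 − k), with an upper limit of 100% when k = 20.

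| Assumed q | Self-applied | Exact 95% CI |
|---|---|---|
| 0% | 20/20 | 83–100% |
| 10% | 18/20 | 68–99% |
| 25% | 15/20 | 51–91% |
| 50% | 10/20 | 27–73% |

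The log would be the same in all four rows.

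**The case against.** The strongest reply has three parts.

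First, the trial does assess patients' own ability, through the checklist, the final test and the repeated practice-device assessments, so the objective is not without evidence. This stands, and it limits the point. But those checks are supervised and made in clinic, whereas the question is about use at home. Since caregivers may be trained instead of patients, it is also unclear whose competence is certified in a household where the caregiver runs the sessions.

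Second, the article never makes the log the measure of self-application. It is used for remote monitoring, for calls after missed sessions and for records. That is correct. A reader might infer that a caregiver-run participant would be counted as a successful self-user, but no such counting rule is written. What can be said is that the log, the only session-level record of use described, cannot answer the question.

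Third, the items of the post-session questionnaire are not listed and the full protocol is not shown, so the operator may already be recorded. This also stands, and the remedy is made conditional on it. The contradiction in the article's text remains either way.

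A reader might also infer that inability to self-apply is removed by the completers-only rule or by the device test. The documents do not support this. The Statistical methods section limits that rule to the efficacy analyses and reports side effects for all participants. Randomization follows screening, before the device test, and nothing says that failed tests go unreported.

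**Conclusion.** The concern holds in this limited form. The article contradicts itself on who operates the device at home, on a matter it names as an objective, and its description of the log gives no means of telling patient-applied from caregiver-applied sessions. The confidence is high for the contradiction. It is lower for the missing operator record, because the full protocol may contain one.

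The size cannot be computed from the document, because no caregiver share is given. Under assumed shares from 0% to 50%, the same complete logs would be compatible with anything from 20 of 20 to 10 of 20 true self-users.

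It would be too strong to say that the cognitive results are compromised. Stimulation placed by a caregiver still delivers the assigned condition, so the primary comparison of active with sham is not directly affected. The change should be made for the self-application objective alone.

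**What to change.** 1. Make the Abstract, the Background, the tDCS stimulation protocol section and both treatment phases of the Study schedule agree on who may operate the device at home. Which rule to adopt is for the sponsor and investigators. If caregiver use is permitted, the objective and the Discussion should be worded to match.
2. Unless the full protocol already records it, add one item to the existing post-session smartphone questionnaire on who placed and started the device: patient alone, patient with help, or caregiver.
3. Report patient-alone and caregiver-applied sessions separately, with assisted sessions as their own category.
4. Base the self-application result on all participants who entered device training, including those who failed the test or stopped.

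The cost is one extra question per session and some protocol wording, and the self-application rate may look lower than a count of logged sessions. The Trial status section has recruitment running from March 2018 to July 2019, so the new item can cover only sessions still to come. Earlier sessions without an operator record should be shown as not recorded, not counted as self-applied.

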### Statistical analysis

#### Sample size

The sample size was calculated based on results reported by Boggio et al. [12]. Boggio et al. [12] administered active or sham tDCS once daily for 5 days to patients with Alzheimer’s dementia and compared their performance for visual recognition tasks before and at 1 month after treatment. Based on differences in mean correct response rate (ε = 11.61, σ_d_ = 11.62; 1:1 allocation ratio per group) in the previous study, a sample size was estimated to obtain at least 90% power (1 − beta = 0.9) to detect a treatment difference of 11.61 (SD 11.62 of change) in visual recognition task scores at a significance level of 0.05 (α = 0.05). A total of 14 persons (seven per sequence) were selected by PASS 12 (NCSS, LLC, Kaysville, Utah, USA, https://www.ncss.com/) as the smallest sample size. This study targeted a total of 20 subjects (10 per group) considering a drop rate of 30%.

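### The interval from the last home session to the T2 and T4 efficacy tests is not fixed, and the stated session and visit days allow it to differ between periods

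*Protocol article*

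**What the plan says.** All of this is in the protocol article.

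- **Time of day (Study schedule).** "It is recommended to use the device at specific times (e.g., immediately after face washing in the morning"; this is advice with one example. The device stores application times automatically, and researchers monitor use remotely and call if a session is missed.
- **Period I (Study schedule).** A first application takes place in the clinic at T1. Home use starts the following day and continues once daily for 14 days.
- **T2.** The text says: "The subject will be required to visit the hospital 2 weeks after visit T1 for efficacy assessment". Table 1 puts T1 on Day 1 and T2 on Day 14.
- **Period II (Study schedule).** "After returning home, subjects will apply the device once daily for 2 weeks (14 days". The preceding sentence describes home use in this period as like that in treatment I.
- **T3 and T4.** Table 1 gives Days 28 and 42; the text gives 4 and 6 weeks after T1.
- **Primary analysis (Statistical methods).** The endpoint is the change in correct response rate from before to after each treatment. A general linear model assesses treatment, period and carry-over. The Discussion offers the carry-over analysis as the answer to a wash-out that may be too short.
- **Duration of effect.** The Background cites a study in which "tDCS can result in temporary but meaningful improvement in aging-related cognitive decline", and gives the effect of repeated sessions in MCI as the question to be answered. The Discussion says effects have been reported to continue in Alzheimer's disease.

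**The concern.** The trial sets out to measure what a two-week course does. If the test is sometimes taken hours after a session and sometimes about a day after, the change score may contain a varying amount of any short-lived response to the latest session.

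If the lag varied only between patients, this would mainly blur what the estimate means. A lag that differs systematically between periods is more awkward. Active-first patients would have active stimulation read at one lag, and sham-first patients at the other. That is a treatment-by-period interaction, and a two-period, two-sequence cross-over cannot separate it from carry-over. Both the treatment estimate and the authors' safeguard against an insufficient wash-out would be affected.

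**Working it through.** **1. The planned sample size, for reference.** Inputs from Sample size and Randomization and blinding: "at a significance level of 0.05" (two-sided assumed), "a sample size was estimated to obtain at least 90% power", "to detect a treatment difference of 11.61 (SD 11.62 of change) in visual recognition task scores" and "Participants are allocated 1:1 to the active first group and sham first group". I take 11.62 as the SD of the within-patient difference.
- Normal approximation: N = (11.62 × (1.960 + 1.282) / 11.61)² = 10.53, so 11.
- Noncentral t with N − 2 degrees of freedom: power 0.876 at N = 12, 0.906 at 13 and 0.929 at 14. The smallest even N is 14, as stated.
- Dropout: 14 / (1 − 0.30) = 20, as stated.

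Nothing below changes this.

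**2. The calendar, with T1 on Day 1.** The clinic application at T1 is counted separately, because the text starts the 14 home days on the next day.

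| | Home sessions | Test day | Morning user at the test |
|---|---|---|---|
| Period I, T2 per Table 1 | Days 2-15 | 14 | 13 home sessions done, last one hours earlier; the 14th falls after the test |
| Period I, T2 per text (1 + 14) | Days 2-15 | 15 | 14 done, last one hours earlier |
| Period II, starting on the day of T3 | Days 28-41 | 42 | 14 done, last one about a day earlier |
| Period II, starting the day after T3, as in period I | Days 29-42 | 42 | 14 done, last one hours earlier |

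Counting T3 and T4 as exact weeks from T1 moves them to Days 29 and 43. They stay 14 days apart, so the period II lags do not change. A patient who stimulates in the evening is tested the day after the last session at both visits, on either reading of period II.

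**3. Effect of a lag that differs by period.** Let d be the course effect and a an extra short-lived effect of active stimulation, present at T2 in every patient on active and gone at T4. Expected changes, leaving out a common period effect (which cancels):
- Active-first: d + a in period I, 0 in period II.
- Sham-first: 0 in period I, d in period II.

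Treatment estimate (usual within-patient contrast) = {[(d + a) − 0] − [0 − d]} / 2 = d + a/2.

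Carry-over contrast (sum of both changes, active-first minus sham-first) = (d + a) − d = a, with no true carry-over.

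**4. Illustration.** The documents give no value for a, so 10%, 25% and 50% of 11.61 are assumptions. For the carry-over test, the SD of the summed changes is 11.62 × √[(1 + ρ)/(1 − ρ)] and the standard error is that SD × √(4/N). The correlation ρ between the two change scores is assumed to lie between 0.5 and 0.

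| a (points) | Shift in treatment estimate | False carry-over contrast | Carry-over test rejects at 0.05, N = 20 | Same, N = 14 |
|---|---|---|---|---|
| 1.16 | 0.58 | 1.16 | 5.2-5.5% | 5.1-5.3% |
| 2.90 | 1.45 | 2.90 | 6.1-8.3% | 5.7-7.2% |
| 5.81 | 2.90 | 5.81 | 9.4-18.5% | 7.9-13.8% |

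For each a these shifts are upper bounds, because step 3 gives every patient the full lag difference.

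**The case against.** The strongest reply has five parts.

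*The difference between periods is one reading only.* This stands. If period II starts the day after T3, as in period I, a morning user is tested on the day of a session in both periods. Evening users show no difference either way. A reader might infer that the plan builds in hours at T2 against a day at T4; the text permits that but does not prescribe it.

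*The timing is not left uncontrolled.* This stands in part. A regular time is advised, use is monitored and application times are logged. These measures show when a session was done, but they set no interval to the test. Visit-hour rules may be in the full protocol (version 1.1) or the schedule figures, which were not available for this check. The conflict among the days in the article's own text and table remains.

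*An acute after-effect is assumed.* This stands. The Background remark on temporary improvement concerns another study, in aging-related decline, and gives no duration. The sample size rests on results one month after treatment. The documents therefore do not show that the endpoint does contain an acute effect.

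*The comparison with sham is protected.* This stands. Active and sham follow the same timing within a period and the order is randomised. If stimulation does nothing, a is zero and there is no false-positive inflation. Nor does Statistical methods attach any decision to the carry-over result.

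*Readings away from stimulation exist.* The task is repeated at T3 and F1, two weeks after T2 and T4. It would therefore be too strong to say that a benefit could never be credited to the course. These readings help to judge persistence, but the primary contrast still rests on T2 and T4.

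**Conclusion.** The concern holds in a limited form. The article sets no interval from last session to efficacy test, and its session and visit days do not agree. In period I the test falls inside the course or on its last day. In period II the course ends on Day 41 or Day 42, with T4 on Day 42. The plan as written therefore allows the lag to differ by period.

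The consequence depends on a short-lived after-effect whose size the documents do not give. If present at T2 only, it moves the treatment estimate by a/2 and the carry-over contrast by a: at most 2.90 and 5.81 points if a were half of the planned difference. The chance of a false carry-over signal stays close to nominal unless a is large. What is at stake is which effect is being averaged and how cleanly the carry-over check can be read. The validity of the randomised comparison and the sample size are not in doubt.

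**What to change.** 1. The sponsor should reconcile the first and last session days of each period, and the days of T2, T3 and T4, between the Study schedule text and Table 1. Which days are right is for the sponsor to settle.
2. Book the T2 and T4 efficacy tests at the same interval after the last session in both periods, and verify it from the logged application times.
3. For patients already treated, report the logged interval by period and treatment, and explore it as a covariate in a sensitivity analysis. Do not exclude same-day tests: if most patients stimulate in the morning, that could remove most period I data from a trial of 20.

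The cost is a booking instruction and the use of times the device already stores. The downside is slightly less freedom in scheduling visits. With 20 patients the covariate analysis will be imprecise and should be presented as exploratory.
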